**Figure 1 F1:**
[figure not shown]
Overview of the study cohorts, their expected age of entry into each school year and the available data. A&E, accident and emergency; HES, Hospital Episode Statistics; NPD, National Pupil Database; ONS, Office for National Statistics.

### Defining key study measures

#### Defining neurodisability in administrative records

We propose two complementary approaches based on health and education data recorded in HES and in NPD to identify adolescents with neurodisability before the start of secondary school (Year 7), ensuring that all exposures are measured before the outcomes. Ensuring exposures are measured before outcomes reduces the risk of reverse causality, where the outcome might influence the exposures. Although this is descriptive work, maintaining this temporal sequence helps establish a clear direction of influence. Throughout the protocol, we refer to children with neurodisability recorded in HES and NPD as ‘children with neurodisability’, although we note that some children with neurodisability are likely to be omitted in the absence of linkage to other datasets (including primary care or community paediatrics) or because their difficulties have not been identified by any service.

We will use a phenotyping algorithm for indicating conditions with high risk of neurodisability from diagnostic data recorded in HES admitted patient care records developed as part of the HOPE Study.^16^ This list includes conditions such as cerebral palsy, epilepsy, autism, learning disabilities, muscular dystrophies and other neurologic conditions associated with high risk of functional impairment (such as hydrocephalus, brain tumours or indicators of infection or inflammation of the brain).^1 8 12 38 39^ We will use diagnostic data from all hospital admissions before entry to Year 7. We will examine recording of included conditions in adolescents and consult expert clinicians to derive clinically meaningful subgroups of conditions with comparable health and educational needs and functional impairment. These subgroups could include: (1) intellectual and developmental disorders; (2) autism spectrum disorder; (3) cerebral palsy; (4) epilepsy; and (5) genetic and chromosomal conditions.

As adolescents with neurodisability receive much of their care outside of secondary healthcare settings (ie, in community paediatrics, primary care), some conditions are likely to be under-reported in hospital records (eg, autism or hyperkinetic disorders).^12 40^ We will therefore complement information from hospital records with information on types of need for SEN provision recorded during primary school to increase case ascertainment. This approach has been used previously in linked health and education data from Scotland^18 41^ and in studies based on education data only in England.^20 42 43^ We will examine recording of likely autism and learning disabilities using information on primary and secondary type of need for SEN provision in primary school records (Years 1–6, aged 5/6–10/11 years old). Learning disabilities will be indicated by combining three types of SEN (categorised in an ascending hierarchy): (1) profound and multiple learning difficulties (where children are likely to have severe and complex learning difficulties as well as a physical disability or sensory impairment); (2) severe learning difficulties (where children are likely to need support in all areas of the curriculum and associated difficulties with mobility and communication); and (3) moderate learning difficulties.^17^ We only use information on type of need collected prior to 2014/2015 education reforms (see figure 1),^17^ ensuring consistency of coding of SEN need over time.

#### Outcome: mortality

As part of descriptive work towards objective 1, we will examine all-cause mortality rates in young people with neurodisability compared with their peers. Mortality will be compared based on the data source used to identify neurodisability (HES vs NPD) and for children with different types of neurodisability. Information on deaths will be obtained from linked Office for National Statistics (ONS) mortality records and supplemented with information on in-hospital deaths recorded in HES. Children will be followed from 1 February of Year 7 until death or 1 March 2020, whichever occurred first.

#### Outcome: educational outcomes

We will describe changes in educational support (measured as school-recorded SEN provision) and school participation (measured by absences and exclusions from school) per year of age across secondary school (between start of Year 7 and end of Year 11, or until loss of follow-up, death or 31 December 2019, whichever occurred first) for adolescents with neurodisability and unaffected peers. Our primary focus will be on persistent absences. Secondary outcomes will be medical/non-medical absences and exclusions. All outcomes are defined in table 1.

**Table 1 T1:** Definitions of educational outcomes

Outcomes		Definition	Dataset(s)	Measured
**School participation**	Persistent absentees	Pupils who miss 10% or more of their possible sessions^45^	NPD School Census	Year 7–Year 11 (11/12–15/16 years old)
	Absence for medical reasons	Authorised/unauthorised absences for doctor/dentist appointments or illness*		
	Absences for non-medical reasons	Authorised/unauthorised absences for all other reasons than medical*		
	Exclusions	Pupils with at least one suspension (fixed-period exclusion) or permanent exclusion in the given school year		
**Educational support**	SEN provision (by type)	SEN provision will be grouped in the following descending hierarchy: No SEN provision SEN support in mainstream school EHCP in mainstream school Enrolment in specialist provision		

* We will use the total number of possible sessions rather than pupils as denominator.

EHCP, Education, Health and Care PlanNPD, National Pupil Database; SEN, special educational needs

NPD data include some information about post-16 educational outcomes (such as special school attendance until 19 years old or education, employment or training at 17–18 years from National Client Caseload Information System),^34^ and we will explore the feasibility of using these data to examine educational trajectories of adolescents with neurodisability after secondary school.

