### Study population and follow-up

We will develop a cohort of secondary school aged adolescents enrolled in state-funded schools in Year 7 (usually aged 11–12 years old) between 2008/2009 and 2014/2015. We will exclude young people who are 2 or more years outside of their expected age for their school year.

Adolescents will be followed up from 1 February (after the spring school census) in Year 7 through to Year 11 (the end of secondary school, usually aged 15–16 years old) in education records, and until aged 22 in healthcare records (due to data availability) (figure 1). Education outcomes will be measured until the end of term 1 of the 2019/2020 academic year (31 December 2019) in education records, the last full academic term before the COVID-19 pandemic. Healthcare outcomes will be measured up until 1 March 2020, just before the first COVID-19 lockdown in England, as the pandemic impacted access to school and the frequency of hospital contacts captured in ECHILD data.^36 37^

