#### Objective 2b: trends in educational support, school attendance and exclusions

We will calculate and plot the proportion of pupils experiencing each educational outcome (defined as the number of pupils with at least one recording of the outcome divided by the number of pupils on school roll at the start of the given school year) by year of age. We will use a Poisson or logistic regression model to quantify the differences between adolescents with neurodisability and their peers. The models will include age, birth year and an indicator of neurodisability, and we will account for repeated measures per child. We will also graphically quantify changes in proportions of adolescents experiencing each outcome according to neurodisability subgroup and sociodemographic characteristics (separately for adolescents with neurodisability and their peers).

Analyses carried out for objectives 2a and 2b will reveal whether support and adverse outcomes across health and education follow similar trajectories with age for adolescents with neurodisability and their peers and illustrate potential inequalities in support and adverse outcomes to inform design of further studies.

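### SEN provision is followed across the 2014/15 reforms with no reform or period term, so part of any shift at the reform would read as a change with age

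*Protocol article*

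**What the plan says.** All references are to the protocol article.

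- **Population and follow-up.** The section on study population and follow-up takes pupils "enrolled in state-funded schools in Year 7 (usually aged 11–12 years old) between 2008/2009 and 2014/2015" and follows them in education records from "1 February (after the spring school census) in Year 7 through to Year 11". Education outcomes stop on 31 December 2019, after the last intake's expected Year 11 (2018/19).
- **Outcome.** The section on educational outcomes says: "We will describe changes in educational support (measured as school-recorded SEN provision) and school participation". This is done per year of age across secondary school. For Table 1, "SEN provision will be grouped in the following descending hierarchy", and the same four levels serve all years.
- **Guard on the exposure.** The section on defining neurodisability says: "We only use information on type of need collected prior to 2014/2015 education reforms". The reason given is "ensuring consistency of coding of SEN need over time".
- **Model.** Objective 2b plots the proportion with each outcome by year of age and fits a Poisson or logistic model: "The models will include age, birth year and an indicator of neurodisability", with an allowance for repeated measures. No reform or calendar-period term is listed, and the plots are not split by period.

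**The concern.** The article accepts that the 2014/15 reforms could make SEN records inconsistent over time, and it restricts the exposure accordingly. The SEN provision outcome crosses the same date without any corresponding step.

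Within each intake, later school years fall in later calendar years. Pooled over intakes, older pupils are therefore observed after the reform more often than younger ones. If the recorded level of provision moved at the reform, a by-age analysis without a period term would show part of that move as a change with age. SEN provision is the only educational-support outcome in Table 1, and its change with age is part of the study's aim, so the curve at risk is one the study sets out to report.

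**Working it through.** The plan gives no figure to reproduce here. The check uses the intake and follow-up dates above and dates the reform to 2014/15. It assumes equal intakes, no attrition, one birth year per intake, and school year standing in for year of age.

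**1. Post-reform observations (intake year + school year − 7 ≥ 2014).** There are 7 intakes × 5 school years. Intakes 2008/09 and 2009/10 are wholly pre-reform, 2010/11 to 2013/14 straddle the reform, and 2014/15 is wholly post-reform.

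| School year | Post-reform intakes | Share |
|---|---|---|
| 7 | 1/7 | 14% |
| 8 | 2/7 | 29% |
| 9 | 3/7 | 43% |
| 10 | 4/7 | 57% |
| 11 | 5/7 | 71% |

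**2. Share of a step that reaches the age contrast.** For a step S with no true age effect, the Year 7 to Year 11 difference is (5/7 − 1/7) × S = 4/7 S, or 57%. Regressing the post-reform indicator on school year and intake gives the same 0.571 (0.143 per year).

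**3. Why birth year does not help.** Every intake supplies every school year once, so birth year is balanced over school year. A Poisson model with both factors reproduces the margins, and its age ratio equals the crude one. With post/pre ratio r:

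Year 11/Year 7 = (2 + 5r)/(6 + r)

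| Assumed r | Calculation | Spurious ratio | With post-reform term |
|---|---|---|---|
| 0.9 | 6.5/6.9 | 0.942 | 1.000 |
| 0.8 | 6.0/6.8 | 0.882 | 1.000 |
| 0.7 | 5.5/6.7 | 0.821 | 1.000 |

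**4. Logistic version.** Assumed proportions with no age effect, terms for school year and intake:

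| Pre to post | Spurious Year 11 vs Year 7 odds ratio | With post-reform term |
|---|---|---|
| 20% to 18% | 0.93 | 1.00 |
| 20% to 15% | 0.82 | 1.00 |
| 60% to 50% | 0.79 | 1.00 |
| 20% to 25% | 1.18 | 1.00 |

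The last row shows that an upward shift gives a spurious rise.

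**5. Timing.** If 2015/16 is the first affected year, the shares run from 0/7 to 4/7, again a difference of 4/7. The four odds ratios become 0.83, 0.93, 0.79 and 1.19 for 20% to 15%, 20% to 18%, 60% to 50% and 20% to 25%.

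**6. Group comparison.** In the Poisson model with assumed levels of 60% (neurodisability) and 20% (peers) and a common proportional step of 0.9, 0.8 or 0.7, the group rate ratio stays at 3.00, and added age-by-group terms are all 1.00. It takes a differential step to disturb this. With assumed steps of 0.95 (neurodisability) and 0.75 (peers), the Year 11/Year 7 ratios are 6.75/6.95 = 0.971 and 5.75/6.75 = 0.852. The group ratio then appears to rise by 0.971/0.852 = 1.14, or 14%, if an age-by-group interaction is fitted.

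**The case against.** The strongest reply is that nothing in the article says recorded provision moved at the reform. The guard concerns type of need, a different variable from whether support is provided, so a discontinuity in one does not establish a discontinuity in the other. This stands. The bias is conditional, of unknown size and sign, and zero if there was no shift.

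Other points also stand. The objective 2b model is used to quantify differences between groups, and a common proportional step leaves that rate ratio alone. Persistent absence, not SEN provision, is the named primary focus among the educational outcomes. Getting exactly 1.00 after adding the indicator is partly built in, because the illustrative data contain one step and no other period effect. It shows that a step can be separated from age when four intakes straddle it, not that a single 2014/15 step is the right form.

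Two replies carry less weight. One is that the study is descriptive, so the proportions are true of these cohorts whatever caused them. That is so, but the stated aim is to describe change with age, and a by-age curve that mixes two policy periods in changing proportions will be read as such. The other is that the supplemental appendix or a full analysis plan may deal with the matter. It may, and the appendix on sources of bias is not shown. But the article itself lists the model terms and handles this reform for the exposure, so the point concerns a stated choice and not an omitted detail.

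**Conclusion.** The point holds as a conditional, partial confounding of the absolute age trend in SEN provision. If the recorded level shifted at the reform, about 57% of the shift would appear as a Year 7 to Year 11 change, with or without birth-year adjustment. That gives spurious ratios of 0.94, 0.88 and 0.82 for assumed post/pre ratios of 0.9, 0.8 and 0.7. The figures rest on equal intakes, no attrition and a single step.

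A reader might infer more than the documents support:

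- **That the whole shift becomes an age effect.** In the pooled analysis 4/7 of it does.
- **That provision is known to have fallen at the reform.** The article gives neither size nor direction.
- **That the gap between groups is distorted.** This needs a shift that differs between the groups on the model's scale, and the article offers no evidence of one.
- **That the study's hypothesis could be falsely confirmed.** The introduction treats declining support as the premise and hypothesises that some adverse outcomes may then increase. Objective 2b sets no formal test of a decline in provision.

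It is therefore a cheap improvement and not a must-fix.

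**What to change.** For the SEN provision outcome only:

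1. Add to the objective 2b model an indicator for academic year 2014/15 or later, and its interaction with neurodisability.
2. Plot proportions by age separately for pre-reform and post-reform years.
3. As a check that does not depend on the form of the step, show alone the wholly pre-reform intakes (Year 7 in 2008/09 and 2009/10) and the wholly post-reform intake (2014/15). Neither age curve crosses the reform.

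The cost is two model terms, one extra figure and slightly wider intervals on the age effect. No new data are needed.

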### Additional covariates of interest

We will derive a set of sociodemographic characteristics recorded in or before inception to the cohort in Year 7 (table 2). These include child characteristics (such as gender, ethnic group) and socioeconomic factors (such as area-level deprivation or eligibility for free school meals) which will be obtained from NPD school census. We will use information about hospital admissions before the start of Year 7 to derive indicators of complexity of health needs: coexisting chronic conditions (using all data prior to Year 7) and frequency of healthcare contacts in Year 6 (table 2).

**Table 2 T2:** Sociodemographic characteristics at baseline for pupils in the secondary school cohort

Variables		Definition	Dataset(s)	Measured
**Child characteristics**	Year of birth	Grouped as academic years from 1 September to 31 August	NPD School Census	Year 7 (aged 11/12 years old)
	Month of birth	January to December		
	Gender	Young person’s parent/carer or self-reported gender		
	First language	Young person’s first language (English or other)		
	Ethnic group	Young person’s parent/carer or self-reported ethnicity		
**Socioeconomic factors**	Index of Multiple Deprivation quintile	Quintile of area-level deprivation based on young person’s residential address		
	Free school meals	Eligibility for free school meals (yes or no)		
**Indicators of complexity of health needs**	Chronic conditions (excluding neurodisability)	Presence of chronic conditions^46^ indicated from diagnoses recorded during any hospital admission before the start of secondary school	HES APC	Aged 0–11 years old
	Frequency of healthcare contacts	Number of planned/unplanned hospital admissions, accident and emergency (A&E) attendances and outpatient appointments	HES APC,OP,A&E	Aged 10–11 years old (Year 6)

APC, admitted patient care; HES, Hospital Episode Statistics; NPD, National Pupil Database; OP, outpatient care

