### Statistical analysis

#### Objective 1: descriptive analysis

We will derive point prevalence of neurodisability at the start of Year 7 (defined as the number of pupils with a hospital or school record of neurodisability at any point before they entered Year 7 divided by the number of pupils enrolled in Year 7), overall and by neurodisability subgroup. Children with neurodisability are more likely to live in more socioeconomically disadvantaged households, experiencing multiple social determinants of health which may affect their underlying health needs as well as their access to support services. We will describe numbers and percentages for adolescents according to baseline sociodemographic characteristics (table 2) to understand potential overlaps in factors contributing to health inequalities. NPD and HES are likely to capture adolescents with different levels of health need, we will therefore also describe the overlap and baseline characteristics of adolescents with neurodisability captured in education and health datasets. We will also compare mortality rates in adolescents with neurodisability, overall and according to data source used as a crude measure of complexity of health needs.

ECHILD does not capture termly data on children and young people educated in the private sector (approximately 7% of pupils in England each year).^34^ We will estimate the number of adolescents lost at the start of Year 7 due to being educated outside of state-funded schools. This is defined as the difference in the number of pupils ever enrolled in state-funded primary school and alive in Year 7 and the number of adolescents enrolled in Year 7.

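### The Table 2 chronic-condition row can be positive only in pupils who were admitted, which all hospital-identified pupils were, so its contrast by data source partly reflects opportunity to be coded

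*Protocol article*

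**What the plan says.** Under *Additional covariates of interest*, the protocol article states: "We will use information about hospital admissions before the start of Year 7 to derive indicators of complexity of health needs". Table 2 defines the chronic-condition indicator (neurodisability excluded) as "indicated from diagnoses recorded during any hospital admission before the start of secondary school". It gives HES APC as the only dataset and ages 0–11 as the window.

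Under *Defining neurodisability in administrative records*, the hospital route to neurodisability rests on "diagnostic data recorded in HES admitted patient care records", and the look-back is stated as: "We will use diagnostic data from all hospital admissions before entry to Year 7". The school route uses "information on primary and secondary type of need for SEN provision in primary school records", which requires no hospital contact. A pupil counts as a case through either route: the prevalence numerator under *Objective 1: descriptive analysis* is the "number of pupils with a hospital or school record of neurodisability at any point before they entered Year 7".

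The same section gives the reason for describing cases by data source: "NPD and HES are likely to capture adolescents with different levels of health need". It then plans to "describe the overlap and baseline characteristics of adolescents with neurodisability captured in education and health datasets". The abstract also plans a comparison of children with and without neurodisability at baseline.

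**The concern.** The chronic-condition indicator and the hospital route to neurodisability draw on the same records over the same years. Being HES-identified guarantees at least one admission at which another chronic condition could have been coded. Being NPD-only, or a peer, guarantees none. A never-admitted pupil with a chronic condition managed in primary or community care is counted as having no condition.

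Table 2 labels this row an indicator of complexity of health needs, and the by-source description is motivated by expected differences in need. The row will tend to show that expected difference even where true need is equal, because one group was selected through the records that generate the indicator. At stake is how objective 1 characterises the two ascertainment routes, and how far HES-identified pupils are reported as more complex than NPD-only pupils or peers.

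**Working it through.** The documents give no chronic-condition prevalence and no share of pupils ever admitted, so there is no stated figure to reproduce. The check is an ascertainment calculation.

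**Inputs**
- q: true prevalence of a coexisting chronic condition, set equal in all groups (assumption; 10–30% tried).
- s: probability that the condition is coded, given at least one admission, set equal in all groups (assumption; 0.6–1.0 tried).
- a: share with at least one admission before Year 7. For HES-identified pupils a = 1, from the case definition. For NPD-only pupils (a_N) and peers (a_P) it is an assumption.
- h: HES-identified share of all cases (assumption).

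**HES-identified versus NPD-only**

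Recorded prevalence = q × a × s. The ratio is (q × 1 × s) / (q × a_N × s) = 1/a_N, so q and s cancel.

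| Share of NPD-only pupils ever admitted | Spurious ratio |
|---|---|
| 30% | 1/0.3 = 3.33 |
| 50% | 1/0.5 = 2.00 |
| 70% | 1/0.7 = 1.43 |
| 90% | 1/0.9 = 1.11 |
| 100% | 1.00 |

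Example: q = 30%, s = 0.8 and a_N = 50% give recorded prevalences of 0.30 × 0.8 = 24% (HES-identified) and 0.30 × 0.8 × 0.5 = 12% (NPD-only), with identical true disease.

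**Cases versus peers**

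Only the HES-identified part of the case group is selected on admission. The ratio is [h + (1 − h) × a_N] / a_P. With a_N = a_P = a:

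| h | a = 30% | a = 50% | a = 70% |
|---|---|---|---|
| 20% | 1.47 | 1.20 | 1.09 |
| 50% | 2.17 | 1.50 | 1.21 |
| 80% | 2.87 | 1.80 | 1.34 |

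For instance, h = 50% and a = 50% give (0.5 + 0.5 × 0.5)/0.5 = 1.50. The distortion is smaller than in the by-source contrast and depends on h.

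**Restricting to pupils ever admitted**

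Setting a = 1 in every group gives a ratio of 1.00 under equal q and s. This removes the ever/never part. It does not remove differences in the number of admissions, and so in the number of chances to be coded.

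**The case against.** The strongest reply is that this is one descriptive row.

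- *Other measures of need are planned.* The measure that objective 1 explicitly calls a crude indicator of complexity by data source is mortality, taken from ONS-linked deaths supplemented by in-hospital deaths. Table 2 also counts Year 6 A&E attendances and outpatient appointments. None of these needs a prior admission. This stands, and it confines the mechanism to the chronic-condition row. The Year 6 admission count has a lesser link, where the identifying admission fell in that year.
- *No outcome model uses the indicator.* The objective 2a models name neurodisability, age terms and academic year of birth; the objective 2b models name age, birth year and neurodisability. The planned plots do not name the health-complexity block of Table 2. This also stands. A reader might infer that the rate ratios or later subgroup results inherit the problem, but nothing in the text supports that.
- *The size is assumed.* The window opens at age 0, and the text does not say whether birth admissions count. If they do, nearly all pupils may have been admitted and the ever/never ratio would be close to 1.0. Unequal numbers of admissions would still leave some distortion.
- *The source limitation is disclosed.* The article says that care outside acute hospitals is not captured and that some conditions are under-reported in hospital records. The second statement concerns the conditions used to define neurodisability. Neither says that ascertainment of coexisting conditions differs by identification route. The appendix on sources of bias, cited under *Study design*, is not shown and may address it.
- *Restriction has its own cost.* Admitted NPD-only pupils and peers are a selected subset of a whole-country cohort. That is a reason to add the restricted figure beside the planned row and not to replace it.

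**Conclusion.** The point holds for the chronic-condition row. Both premises are explicit in the article: the indicator requires an admission, and HES identification guarantees one in the same records and window. Differences on this row by data source, and in diluted form between cases and peers, partly reflect opportunity to be coded.

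The spurious HES to NPD-only ratio runs from 3.3 down to 1.0 as the share of NPD-only pupils ever admitted runs from 30% to 100%, assuming equal true prevalence and equal coding once admitted. The documents do not locate the study within that range; the study's own data can.

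A reader might infer that the whole complexity comparison is invalid, or that HES-identified pupils are not truly more complex. The documents support neither. Mortality and Year 6 A&E and outpatient contacts do not depend on this mechanism, and a real difference in need may well exist. The narrower conclusion is that the unrestricted row alone cannot show how large that difference is.

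**What to change.** Keep the planned row. Beside it, for four groups (HES-only, both sources, NPD-only, peers), report:

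1. the share with at least one non-birth admission before Year 7;
2. chronic-condition prevalence among those ever admitted, stratified or standardised by number of prior admissions.

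State whether birth admissions count towards the indicator. Label never-admitted pupils as having no hospital record, not as free of chronic conditions, and do not interpret the unrestricted row on its own as a difference in health need.

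Do not drop the identifying admission in the HES group only. That would require two admissions of those pupils and one of everyone else, would select a more heavily admitted HES group, and would discard comorbidity coded at that admission in one group alone.

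The cost is a few extra lines in the baseline table, from data already held. The drawback is that the added comparison covers fewer NPD-only pupils and peers, and those it covers are a selected group.
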